### Data Extraction and Synthesis (Structured Data)—Ongoing

To determine whether the targeted structured variables were present in a patient’s record, we identified lists of codes (ie, ICD-9-CM codes) to operationally define the variables. When available, definitions employed by the VHA Support Service Center (VSSC), a centralized reporting portal, were used. The VSSC provides data summaries to VHA administrators and policy makers regarding business operations, clinical care, quality performance, and resource management. Otherwise, operational definitions were obtained from the AHRQ’s HCUP Clinical Classifications Software [20] or the Centers for Medicare and Medicaid Services definitions. Extraction routines were used to identify each occurrence of the variable in the patient’s record. These data were then transformed into single elements in the analytic data table based on clinically relevant temporal considerations. For example, some comorbidities such as diabetes were considered chronic conditions, while others such as fractures were framed in a 1-year period.

### Data Extraction and Synthesis (Unstructured and Semistructured Data)

We will employ NLP techniques to extract targeted information from the documents in the EHR. This will be accomplished using the following steps.

#### Step 1: Create Reference Standard—Complete

Large samples of documents (approximately 2000) will be extracted from the larger corpus of documents. A human-annotated (ie, chart review) corpus will be developed, which will be used as a reference standard to train and evaluate NLP algorithms. An annotation schema was developed, which defines the classes of concepts based on the variables reviewed by the expert panel. The concepts will be annotated in each document in the corpus by two clinicians and adjudicated by a third clinical expert. Interrater reliability will be evaluated by calculating interannotator agreement. Agreement between the two annotators will be evaluated by calculating the *F* measure, proposed by Hripcsak and Rothschild [21], against the final reference that will be adjudicated by our clinical expert.

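### The planned interannotator F measure compares each annotator with the adjudicated reference built from the annotators' own work, so it does not measure agreement between the two

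*Protocol article*

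**What the plan says.** All the relevant text is in the Protocol article, Methods, Step 1 (Create Reference Standard).

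- Corpus: "Large samples of documents (approximately 2000) will be extracted from the larger corpus of documents".
- How the reference is made: "The concepts will be annotated in each document in the corpus by two clinicians and adjudicated by a third clinical expert".
- What it is for: it is a human-annotated corpus "which will be used as a reference standard to train and evaluate NLP algorithms".
- The quantity to be measured: "Interrater reliability will be evaluated by calculating interannotator agreement".
- The statistic: "Agreement between the two annotators will be evaluated by calculating the" F measure.
- The comparator: "against the final reference that will be adjudicated by our clinical expert".

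The article describes no comparison of one annotator with the other before adjudication. It also gives no expected agreement, no threshold for F, and no statement on whether the expert rules only on disagreements or may also add spans and overturn agreed ones.

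**The concern.** The named quantity and the comparator do not match. Interrater reliability asks whether two people, working independently from the same schema, mark the same things. Here each annotator is scored against a standard that the annotator helped to create. If the expert only settles differences, every span that both marked counts as correct for both, including shared errors, and every span that only one marked is decided in favour of one of them.

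This is not a detail left to a fuller document. The article states the comparator, and it is the wrong one for the quantity it names.

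At stake is the only reliability measure the article describes for the reference standard. Table 3 lists concepts on which clinicians can reasonably differ, such as historical, recurrent or negated mentions of an ulcer, moisture, and malnutrition. A low pairwise F on one of these would suggest that the schema needs tightening. A figure pushed towards 1 weakens that signal and gives readers too favourable a view of the standard behind the NLP variables.

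**Working it through.** The plan states no agreement figure, so there is nothing to reproduce. The check is algebra on the F measure, with assumed values shown as ranges.

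**Notation.** Let a = spans marked by both annotators, b = spans marked by A only, c = spans marked by B only. The expert accepts a share p of b and a share q of c. None of these values is in the article.

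**Formulas, if the expert rules only on discordant spans**

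- Pairwise: F = 2a / (2a + b + c).
- A against the reference: F_A = 2(a + pb) / [2(a + pb) + (1 − p)b + qc]. F_B is symmetric.

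**Direction.** Cross-multiplying, F_A − F has the sign of 2ac(1 − q) + 2pb(a + b + c), which is never negative. It is zero only if the expert always sides with B (p = 0, q = 1). F_B equals F only in the opposite case. When b and c are both above zero, the mean of F_A and F_B therefore always exceeds F. A numerical grid over a, b, c, p and q agreed: no individual value fell below the pairwise F, and the mean was above it in every case.

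**Size, with b = c and p = q.** The formula reduces to 2F/(1 + F) at 0% acceptance, (1 + F)/2 at 50%, and 2/(3 − F) at 100%. For F = 0.70 these are 1.40/1.70 = 0.82, 1.70/2 = 0.85 and 2/2.30 = 0.87.

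| Pairwise F | Reported, 0% accepted | 50% | 100% |
|---|---|---|---|
| 0.50 | 0.67 | 0.75 | 0.80 |
| 0.60 | 0.75 | 0.80 | 0.83 |
| 0.70 | 0.82 | 0.85 | 0.87 |
| 0.80 | 0.89 | 0.90 | 0.91 |
| 0.90 | 0.947 | 0.950 | 0.952 |

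**When the direction reverses (b = c, 50% acceptance).**

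- Suppose the expert adds spans that both annotators missed. The reported F equals the pairwise F when the added spans make up a share 1 − F of the reference: 30% at F = 0.70 and 10% at F = 0.90.
- Suppose instead the expert overturns agreed spans. The break-even share of agreed spans is (1 − F)/[F(2 − F)]: 0.30/0.91 = 33% at F = 0.70 and 0.10/0.99 = 10% at F = 0.90.
- Beyond these points the reported figure understates pairwise agreement.

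**Attributes with several values.** Table 3 has attributes such as laterality and assertion, where two annotators can differ and the expert can choose a third value. If every disagreement ended that way, each annotator would have d wrong values (b = c = d) and miss d reference values. Then F_A = 2a/(2a + 2d), which is the pairwise F, so there would be no inflation. If only some disagreements end that way, the inflation shrinks but does not reverse.

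**The case against.** The strongest reply is that this is mostly a labelling fault with little consequence. Several parts of that reply stand.

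- No later step uses the agreement figure. The article sets no threshold, retraining rule or exclusion on it. The adjudicated reference, the 70/30 development and validation of the pipeline in Step 2a, and Hypotheses 1 to 3 are the same whichever F is reported.
- The expert sees the disagreements while adjudicating, so ambiguous concepts are not invisible to the team. What is lost is a correct summary for the team and for readers.
- F against the reference is a legitimate figure. NLP output is scored against the same reference, so it is a natural human comparison, although annotators whose work fed the reference have some advantage. This is a reason to keep it under another name.
- The upward direction is conditional, as the working shows, and at high agreement the gap is only about 0.05.

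A reader might go further and infer that an overstated reliability figure taints the 829 ulcers identified from text alone (Sample and Sampling). The documents do not support that. That section is marked complete and already reports the 829, while Results describes annotation and adjudication as ongoing. Nothing says that this reference standard trained the classifier behind those cases.

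The reply does not remove the central point. Whatever the expert's remit, F against the reference is not agreement between the two annotators, and the article says that it is.

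**Conclusion.** The point holds in a limited form. Step 1 promises interrater reliability and specifies a statistic that measures each annotator's conformity with a standard derived from their own annotations. That mismatch is in the text and needs no assumption.

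That the figure is too high rests on adjudication mainly resolving disagreements, which is the natural reading but is not stated. On that reading, with equal unique spans, the overstatement is roughly 0.12 to 0.17 at a pairwise F of 0.70 (0.82 − 0.70 to 0.87 − 0.70) and about 0.05 at 0.90. The article gives no basis for choosing among these values.

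It would be going too far to say that the bias is certainly upward, or that the comparisons of the risk models are altered. The first depends on the expert's remit. The second does not follow, because those comparisons do not use the agreement figure. The correction is worth making because it concerns the stated quality of the standard that trains and tests the NLP variables used in Hypotheses 2 and 3.

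**What to change.** In Step 1, calculate the F measure directly between annotator 1 and annotator 2 on their independent annotations as they stood before adjudication, by concept, and report that as interrater reliability. Keep F of each annotator against the adjudicated reference as a second figure, labelled annotator accuracy. It would also help to state whether the expert rules only on disagreements or may add and overturn spans, since that governs how the second figure is read.

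The cost is small. The planned calculation already needs each annotator's own markings, so no new annotation is required provided that the pre-adjudication versions are kept. The step is headed as complete, but Results says that annotation and adjudication are continuing, so retention should be confirmed now. The price is that the reported reliability will probably be lower.

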#### Step 2: Extract Information From Unstructured and Semistructured Text Data—Ongoing

We will use the annotated reference set of documents to develop and evaluate distinct methods to extract information from unstructured and semistructured text.

##### Step 2a

The General Architecture for Text Engineering (GATE) software will be used to create an NLP pipeline to extract the information from the unstructured text data [22]. The results of the NLP pipeline will be iteratively compared to the annotated terms from the reference standard on 70% of the documents. The remaining 30% of the documents will be used to validate the best model. This will enable the pipeline to be iteratively refined to more accurately identify the potential predicators located in the narrative documents.

##### Step 2b

We will develop an NLP system for semistructured text data. The composition of semistructured text presents unique challenges to NLP, making information extraction especially challenging [23,24]. Semistructured text consists of short, simple phrases that are not grammatically correct.

A traditional grammatical NLP system may fail to negate the presence of moisture for the patient. While this “structure” aids readability, it hinders traditional grammatical NLP systems. However, this “structure” makes rule-based systems using regular expressions a viable alternative for extracting targeted information. Thus, we will employ a custom-developed, rule-based system using named entities- and structural-based regular expressions, which will also be developed and evaluated using an annotated reference set of documents.

### Data Analysis—Planned

Three separate predictive models of PrU occurrence based on each set of predictors in each hypothesis will be developed using R statistical program version 3.3.2 (The R Foundation). To prepare, the distribution of each continuous predictor will be examined and variable transformation will be carried out as appropriate to approximate normality (eg, log transformation of skewed data). However, to avoid information loss, no continuous variable will be categorized in an initial prognostic model. Using the generalized additive model (GAM) approach, a bivariate logistic regression will be performed to test potential nonlinearity between each continuous candidate predictor and the binary PrU outcome [25]. This will provide further guidance for appropriate transformation needed for the predictor.

The analytic data sample (N=12,344) will be randomly divided into two groups in the ratio of 70% (n=8641) for derivation and 30% (n=3703) for validation. The randomization will be stratified by site, age group, and gender to increase similarity in the distribution of both validation and derivation random samples.

### Model Development

An automated model selection procedure will be performed with the R package *glmulti* [26] to select variables and interaction terms in a logistic regression model of PrU status in the training sample. The automated model selection procedure will return a set of *n* best models, ranked by their information criteria values as well as estimating importance scores for the predictors. Thus, it offers us the flexibility to select from the set a more parsimonious or more intuitively reasonable final model that is context based. Another consideration is for the final prognostic model to include variables that could be easily assessed in practice and with minimal burden on the respondent SCI patients. The fully specified prognostic model will eventually be part of an automated decision support system.

The clinical utility of the risk scores will be evaluated for different risk thresholds and the sensitivity, specificity, positive predictive value, and negative predictive value will be included as performance measures in the automated output. In addition, a separate listing of risk factors will be provided for each risk model and ranked by their rounded Z-scores (or standardized regression coefficients). A higher Z-score implies a more “important” contribution of that variable in the model. These lists will assist the clinicians in prioritizing what variables to assess. Each product will be accompanied with appropriate complete operational definitions and scoring instructions.

Data analysis will be focused on testing two hypotheses that compare the ability of the current standard risk assessment measure—Braden Scale—with models based on structure data alone and in combination with data extracted from text. Comparisons will be made between a pair of risk models to test each hypothesis using exactly the same veterans from the validating sample. Our priority will be to develop models with low false positive rate (ie, the rate at which negative instances are incorrectly classified as having PrU). This consideration will guide how any two competing risk models (ie, classifiers) will be compared using the receiver operating characteristic (ROC) curve analysis. The logistic model will output proper probability scores from which a full ROC curve will be generated for each classifier with overlay in one plot. Generally, a higher calculated total area under the curve (AUC) implies a better prognostic performance. However, when comparing two classifiers, it is possible for the classifier with a higher total AUC to show poorer local performance in our priority region. Therefore, we will assess classifier performance in the overall AUC as well as partial AUC (pAUC) in our priority local region of low false positive rate. The classifier that has a higher sensitivity (ie, true positive rate) in the priority region has superior local performance. That is, an appropriate pAUC will also be computed in addition to the standard full AUC.

Both discrimination and calibration will be investigated as validation measures for each prognostic model using the validation sample. The better discriminating models have higher AUC and pAUC values based on their CIs (ie, better able to distinguish between patients with SCI who have and do not have PrU). To assess calibration, the predictions of each model will be compared with the veterans’ actual outcomes in the validation sample by performing the Hosmer-Lemeshow test using the hoslem.test function in the Resource Selection library of R. To ensure that the overall type I error rate of α is maintained, first, we will repeatedly sample from each model and calculate the Hosmer-Lemeshow *P* value 1000 times, and calculate the proportion of *P* values less than .05 (ie, type I error rate should be no greater than 5%).

A graphical approach will be used to compliment the Hosmer-Lemeshow test since it has been known to be sensitive to sample size. For the graphical method, first, the sample will be divided into 10 risk groups of equal size with each group having similar model predicted probabilities. Next, the observed proportions of PrUs will be plotted against predicted probabilities for these groups with one smooth curve fit (eg, lowess) as well as a linear fit to the data points. We anticipate that the observed and predicted occurrence of PrUs will be similar across the risk groups. A perfect calibration (ie, perfect agreement between the predicted and observed outcomes) will produce a calibration line with an intercept and slope of 0 and 1, respectively [27-29]. The smooth curve will be added to reveal differential calibration among risk deciles, if present.

We expect the validation study to span across different domains (eg, inpatient vs outpatient, site, age group, and gender) as this provided the strongest evidence of generalizability of the prediction rule to new patients [30]. Since stratified randomization ensured a similar case mix within each of our samples—derivation and validation—and both samples were representative of our population of interest, we believe that the results of our validation tests will serve as strong evidence of generalizability.

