### Variables Selection and Definition—Ongoing

The dependent variable for this study will be documentation of the occurrence of a PrU in the EHR within 1 year (ie, 1-year incidence risk of PrU). The definition of the presence of a PrU used for case identification is based on ICD-9-CM codes (707.0-707.9) and the application of the classification algorithm based on text analysis or a combination of these two sources, depending on what is found to be more accurate. The potential independent variables for this study include the risk factors that were identified through a literature review and validated by expert panel discussion. The final list of potential risk factors, with input from the expert panel, will be extracted from multiple tables in the EHR, or from semistructured and unstructured text notes, for use in analysis. Three sets of candidate predictors based on data sources will be generated to develop each risk model: (1) structured data extracted directly from the EHR, (2) Braden scores, and (3) a combination of existing structured data and data extracted from text through the NLP processes.

The investigators conducted a comprehensive literature review generating a list of approximately 50 potential independent variables or risk factors (eg, demographics, diseases status, comorbidities, health behaviors, psychosocial factors, and home care). This list was reviewed by the expert panel for logical consistency, completeness, clinical relevance, and whether they were modifiable or not. The panel identified high-priority risk factors and discussed practical considerations including where the risk factor might be located in the EHR, how reliable these data might be, and alternative ways to document risk factors. Subsequently, persistent moisture on the skin, the type of living situation of the patient, evidence of malnutrition, and documentation that the patient took steps to redistribute their weight during the day were targeted as risk factors available in unstructured data. Structured data contained elements of the Braden Scale, lab values, and other variables (see Table 1). Several coding systems are used to classify structured data variables, including the ICD-9-CM, Logical Identifiers Names and Codes (LOINC), and the Healthcare Common Procedural Coding System (HCPCS). International Classification of Diseases, Tenth Revision, Clinical Modification (ICD-10-CM) codes were not implemented in the VHA until after the end of this study and are not used.

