### Sample and Sampling—Complete

Using VHA data in its Corporate Data Warehouse obtained through its Veterans Affairs Informatics and Computing Infrastructure (VINCI), we identified an inception cohort (N=12,344) of veterans with SCI who received care in the VHA in FY 2009, but had no PrU in the 12 months prior to 2009 based on recorded ICD-9-CM codes. This group was considered free of PrUs for the purpose of the study. All structured hospital discharges (N=4090), outpatient encounters (N=5,202,804), and text data (N=9,888,245) for the cohort for FY 2009-2013 (October 1, 2008-September 30, 2013) were obtained through the VINCI. Veterans from this cohort were classified as having a PrU (ie, PrU+) or not having a PrU (ie, PrU-) during the study period based on both structured and text data. A total of 3860 PrUs were identified based on structured data and 829 based on text data alone, resulting in a total incidence of 4689 (4689/12,344, 37.99%) across the study period.

**Table 1 table1:** Risk factors categorized by structured, semistructured, and unstructured data sources.

Data source	Risk factor	Description or definition
Structured	Age	Age in years
	Gender	Male/female
	Race/ethnicity	Race/ethnicity
	Education level	Highest level of education
	VHA^a^ eligibility	VHA category, service connection
	Body weight	Body mass index, most recent weight, or change in weight
	Patient status	Inpatient/outpatient when pressure ulcer develops
	Pattern of preventive care	Consistency of annual well-patient exam
	Cognitive dysfunction	ICD-9-CM^b^ codes (ie, traumatic brain injury, dementia, and Alzheimer’s disease)
	Comorbidities—psychological	ICD-9-CM codes (ie, depression, anxiety, and posttraumatic stress disorder)
	Comorbidities—physical	ICD-9-CM codes (ie, diabetes mellitus, pulmonary disease, cardiac disease, renal disease, peripheral vascular disease, anemia, deep vein thrombosis, cancer, infection, lower extremity fractures, spasticity, autonomic dysreflexia, hypotension, and heterotopic ossification)
	Laboratory analysis	LOINC^c^ codes for lab values (ie, C-reactive protein, white blood cells, erythrocyte sedimentation rate, renal function, hemoglobin, hematocrit, albumin, and prealbumin)
	Medications	VHA formulary to identify chemotherapeutics, steroids, and benzodiazepines
	Surgery	ICD-9-CM codes of surgical procedures within previous 6 months of pressure ulcer development (administrative data)

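### The uncapped, unpenalised search over interactions can overfit the structured and combined models; under an AIC-type criterion this could hide a modest advantage over the Braden model in Hypotheses 1 and 2

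*Protocol article*

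**What the plan says.** Three models are to be built (structured, Braden, structured plus text-derived): "Three sets of candidate predictors based on data sources will be generated to develop each risk model". The literature review is described as "generating a list of approximately 50 potential independent variables or risk factors"; the expert panel then revised that list, and Table 1 shows the result by data source.

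Under Data Analysis, the cohort is "randomly divided into two groups in the ratio of 70% (n=8641) for derivation and 30% (n=3703) for validation". Under Model Development, glmulti is used "to select variables and interaction terms in a logistic regression model of PrU status in the training sample". It will "return a set of *n* best models, ranked by their information criteria values", and the team may then "select from the set a more parsimonious or more intuitively reasonable final model that is context based".

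The section does not say which criterion is used or what limits the interactions, and it mentions no penalty, shrinkage or resampling correction. Hypotheses 1 to 3 are judged on AUC and partial AUC in the held-out 30%, where calibration is also checked by a Hosmer-Lemeshow test and a calibration plot.

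**The concern.** The candidate space differs greatly between the models being compared. A Braden model with six items, or one total score, has almost no room to fit noise. The structured and combined models have hundreds to well over a thousand possible terms once pairs are allowed.

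Chance terms kept in derivation cost discrimination in validation. Because the comparison is made on held-out data, that cost falls on the new models. The first two hypotheses could fail although the structured or combined data really do predict better than Braden. The fitted probabilities would also be too extreme, and the Discussion plans to distribute the model as a clinical tool.

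**Working it through.** **The plan's own figures.** 0.7 × 12,344 = 8640.8 and 0.3 × 12,344 = 3703.2, matching the stated split. 3860 + 829 = 4689, and 4689/12,344 = 37.99%, matching "resulting in a total incidence of 4689 (4689/12,344, 37.99%) across the study period".

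**Candidates (Table 1).** There are 16 structured rows. Five list components: 3 cognitive, 3 psychological and 14 physical conditions, 8 laboratory values and 3 drug classes, 31 in all. The other 11 rows bring this to 42, or 43 if race and ethnicity are counted separately, as in Table 2. The 13 semistructured and 3 unstructured rows bring the combined set to 59. Splitting the rows this way is an assumption.

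**Terms with all pairs**, k + k(k−1)/2:
- structured: 43 + 903 = 946
- combined: 59 + 1711 = 1770
- Braden, six items: 6 + 15 = 21

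**Derivation events.** Five-year: 0.7 × 4689 = 3282. The stated outcome is one-year risk, for which no count is given. A constant hazard gives 1 − (1 − 0.3799)^(1/5) = 9.1%, or about 788 events; one fifth of the five-year events gives 0.7 × 4689/5 = 656.

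| Set | Terms | Events per term, 5-year | Constant hazard | One fifth |
|---|---|---|---|---|
| Structured | 946 | 3.5 | 0.83 | 0.69 |
| Combined | 1770 | 1.9 | 0.45 | 0.37 |
| Braden | 21 | 156 | 37.5 | 31.2 |

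The structured figure stays below 1 while one-year risk is below 946/8641 = 10.9%; the combined figure, while it is below 1770/8641 = 20.5%. With each row of Table 1 as a single term, the sets are 16 (136 terms; 24.1 and 5.8 events per term on the five-year and constant-hazard counts) and 32 (528 terms; 6.2 and 1.5).

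**Chance interactions passing the criterion.** AIC keeps a null 1-df term with P(χ²₁ > 2) = 0.157, so 903 × 0.157 ≈ 142 and 1711 × 0.157 ≈ 269. BIC requires χ²₁ > ln 8641 = 9.06, with P = 0.0026, so about 2 and 4.5. These are ceilings for an exhaustive search. With 50 candidates there are already 2^50, about 1.1 × 10^15, main-effect models, so glmulti cannot visit them all.

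**Simulation.** N = 12,344, split 70/30, 15 true main effects, no true interactions, an independent Braden score, a DeLong test on the 3703, and 40 runs per row (60 for 16 predictors). Selection was by chi-square thresholds, not glmulti. Fifty predictors (1275 terms) is illustrative and lies between 946 and 1770. AUC and power are shown as main effects only / AIC / BIC.

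| Predictors, events, signal | Validation AUC | Braden AUC | Power | Slope, AIC / BIC |
|---|---|---|---|---|
| 50, 38%, strong | 0.724 / 0.691 / 0.724 | 0.616 | 1.00 / 1.00 / 1.00 | 0.60 / 0.94 |
| 50, 38%, moderate | 0.666 / 0.626 / 0.665 | 0.625 | 0.93 / 0.03 / 0.85 | 0.48 / 0.93 |
| 50, 9.1%, strong | 0.734 / 0.674 / 0.731 | 0.629 | 1.00 / 0.55 / 1.00 | 0.42 / 0.92 |
| 50, 9.1%, moderate | 0.666 / 0.604 / 0.661 | 0.636 | 0.25 / 0.00 / 0.20 | 0.29 / 0.85 |
| 32, 38%, moderate | 0.669 / 0.647 / 0.667 | 0.622 | 0.90 / 0.45 / 0.85 | 0.69 / 0.95 |

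With 16 predictors, AIC costs only 0.004 to 0.015 in AUC. The largest fall in power there is from 0.60 to 0.33 (9.1% events, moderate signal).

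**The case against.** - **The criterion is open.** The article does not name it, and the full plan may name it and limit the interactions. Under BIC the AUC loss at 50 predictors is at most 0.005 here (0.005 to 0.008 in a separate run of 8 replicates). This stands, and the point is therefore conditional. But the article does fix the package, the opening to interactions and the ranking rule, so the weakness is more than an omitted detail.
- **One term count cannot serve both models.** A reader might take the 50 factors, hence 1275 terms, as the size of each model. That list is the initial one across all sources, so the text does not support this. The counts from Table 1 keep the asymmetry with Braden, but they depend on how the rows are split.
- **The final model may be much smaller.** The parsimony option and the wish for easily assessed variables point away from hundreds of interactions, and a search that cannot be exhaustive will not find them all. The expected counts are therefore not a forecast of the final model. Still, the option has no rule and works only within a set that the same criterion has already ranked.
- **Held-out comparison is honest.** It measures the models actually built, so any loss is real and conservative, not a false advantage. Overfitting may fail to show a benefit; it does not invent one. The calibration plot would expose a slope of 0.5, but no recalibration is described.

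**Conclusion.** The search as described leaves the structured and combined models open to overfitting in a way the Braden model is not. The held-out comparison would reveal the loss but not restore it.

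The harm is large only if the criterion is AIC-type, interactions are broadly open, and the true advantage over Braden is modest or events are few. At 50 predictors under AIC the simulated AUC loss is 0.033 to 0.062 and the slope 0.29 to 0.60. With a strong signal and 38% events, superiority over Braden was still shown in every run, although the slope was 0.60. Under BIC the effect is small.

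A reader might infer that the new models will certainly overfit, or that Hypothesis 3 is also biased against the combined model. The article supports neither. The criterion is unnamed. Both models in Hypothesis 3 are searched in the same way, and that comparison was not simulated.

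The sizes rest on assumed signal strengths, one-year event counts, a Braden AUC of about 0.62 to 0.64 independent of the other predictors, no true interactions, and thresholds standing in for glmulti.

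**What to change.** Have the expert panel name a short list of interactions before any model is fitted (at most 20, for example). Then do one of the following:

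1. Fit the models in the derivation sample by penalised logistic regression (lasso or elastic net), with the penalty chosen by cross-validation within that sample.
2. Keep glmulti, but with BIC on main effects plus the listed interactions, and apply a shrinkage factor estimated in the derivation sample before validation.

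A separate simulation of 20 replicates per event rate (50 candidates, true AUC about 0.70, no true interactions) supports both parts:

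| Method | AUC and slope, 38% events | AUC and slope, 7.6% events |
|---|---|---|
| All pairs, AIC-type threshold | 0.64, 0.50 | 0.60, 0.20 |
| 20 listed interactions | 0.68, 0.92 | 0.67, 0.79 |
| Penalised main effects | 0.68, 1.01 | 0.68, 1.01 |

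The slope of 0.79 shows that a cap alone may not be enough when events are few.

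The cost is one panel list and, for the first option, a change of R package; no new data are needed. A true interaction left off the list may be missed, and simulations without true interactions do not price that loss. The first option also gives up glmulti's ranked set of models and importance scores. The planned ranking of risk factors would then use standardised coefficients, which Model Development already allows in place of Z-scores. The second option keeps the ranked set and the importance scores.
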